##### Analysis

Analysis will proceed alongside data collection and be based on a Framework approach.^78^ This approach ensures each case is fully accounted for and is regarded as particularly helpful for addressing policy questions. The primary aim of analysis will be to generate an exhaustive list and description of the salient attributes of care (and levels) identified by participants.

The analytic approach will involve the identification of initial themes that are then grouped into main themes and subthemes. Transcripts will be read and re-read, and coded. At least two members of the research team ([name], MM, LR) will participate in all data analysis to reduce bias in the identification and interpretation of themes.

A thematic ‘chart’ will be created to summarise information for each theme to allow cross‐case and within‐case analysis through a process of constant comparison, with particular attention being paid to deviant cases. Analysis will pay attention to the similarity and differences in salient attributes according to where the seizure occurred (home, public), who was there, who made the 999 call, whether the patient had seen a specialist in the prior 12 months, and whether they self-reported an intellectual impairment. Participant quotations (with minor editing where necessary to preserve anonymity) will be presented to illustrate themes and help verify interpretation. QSR International’s NVivo 11 qualitative data analysis software^79^ will be used as a management tool throughout the process.

The attributes nominated during the ranking exercise will be categorised according to the thematic framework, then analysed quantitatively (by [name]) using standardised rank scores.

#### Stage 1c: knowledge exchange event

##### Purpose

It is important the DCE elicits views on ACPs that could plausibly be delivered within the NHS. This event will therefore, early in the project, determine feasibility of the attributes and associated levels that have been identified by service users in Stage 1b.

##### Design

One-day event at which healthcare professional representatives will be shown draft attributes, levels, and choice sets and asked to deliberate each choice. For instance, should Stage 1b indicate service users consistently say they prefer to be transported home by the ambulance service regardless of distance, then representatives would be asked to what constitutes a feasible distance. Our team has previously used this approach.^80^

##### Recruitment

Around n=15 ambulance staff and neurology service representatives. Persons will be recruited from organisations participating in Stage 1a with the help of a sampling framework to ensure representatives come from geographically diverse areas. Representatives will be reimbursed for travel. Those not able to attend will be able to provide feedback remotely.

##### Analysis

With attendees’ consent, the session will be audio-recorded and field notes taken. Feedback will be used to optimise the attribute levels within the DCEs.

### Stage 2

#### Stage 2a: developing the DCE

##### Purpose

Generate DCE questionnaire to elicit patient and carer preferences for post-seizure care and which meets best practice guidance.^72 81^

Once drafted, the DCE will undergo iterative individual pilot testing with ~15 PWEs and carers from the project’s Patient and Public Involvement (PPI) group to check clarity and duration. Pilotees will ‘think aloud’^85^ when making choices, and asked to consider their preferred presentation of attributes (eg, text, pictograms). Sessions will be audio recorded, notes made and refinements made.

#### Stage 2b: formal DCE

##### Purpose

Determine patient and carer preferences for post-seizure emergency care, estimate uptake of different ACPs configurations, and subgroup differences.

##### Design

A representative sample of PWE and informal carers who have visited ED in the last 12 months, as well as those at risk, will be sought to complete the finalised DCE questionnaire. PWE who have uncontrolled epilepsy, but who have not visited ED in the last 12 months will be asked to visit an online survey page and complete the DCE questionnaire using their own internet enabled devices. Due to potentially greater social disadvantage, patients who *have* visited ED in the prior 12 months will have the additional option of completing the DCE during a face-to-face appointment with a researcher who will provide an internet enabled device.

To limit burden, participants will complete DCEs relating to just two seizure scenarios (allocated at random). As well as the DCEs, respondents will report on their demographics, epilepsy, knowledge and fear of seizures and service use. Each participant will receive a £20 shopping voucher.

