##### Recruitment

General Practices in North-West England will identify potential patient participants by searching their epilepsy registers.^86^ Practices will be recruited with the help of the NIHR Clinical Research Network North West Coast. Practices will send ostensibly eligible patients invitation packs via ‘Docmail’ and a repeat invite 2 weeks later to those not responding. Patients not wishing to participate will be encouraged to notify the team and detail their reasons. Eligibility criteria are in table 1.

A definitive sample size calculation depends on the finalised design of the DCE.^87^ To permit decisions regarding recruitment to be made in the meantime we anticipated the design and calculated the required sample size by using Orme’s^88^ formula. Full details are provided in box 1. This indicated 348 PWE (or associated informal carers) would be required, comprising data 174 patients (or associated carers) who have visited ED in the prior 12 months and 174 patients (or associated carers) who have not.

Box 1Sample size calculation for discrete choice experimentsFormula used and factors considered in estimating likely sample size requiredOrme’s formulae: (*n***t***a*)/ *c* must be ≥500, where *n* is number of respondents, *t* number of tasks, *a* number of alternatives per task, and *c* number of analysis cells (for main effects, the largest number of levels for any one attribute).Anticipated discrete choice experiments (DCEs) to involve participants being asked to make (*t*) nine separate choices between (*a*) two care packages and (*c*) three would be maximum attribute levels. Thus, Orme’s formula indicated complete data from n=84 needed.Intend to complete DCEs for three different seizure scenarios, but participants would only complete two, therefore 126 participants required.To allow for variation in the finalised number of choice tasks and levels we increased this to 150 and further inflated it to 174 to accommodate for ~15% of missing data experienced by prior epilepsy DCEs.As an objective was to describe and compare care preferences of two subgroups (patients (and associated carers) who have visited an ED in the prior 12 months versus patients (and associated carers) who have had a seizure in the prior 12 months, but have not visited an ED), 174 patients (and associated carers) who have visited ED in the prior 12 months and 174 patients (and associated carers) who have not, will need to be recruited.Total sample size, thus n=348.

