##### Analysis

Data for the different seizure vignettes will be analysed separately using an error components logit model that allows for a panel of responses from the same respondent. This will determine the importance of the different care attributes for preference and direction of effect (as indicated by the significance of the coefficients and their size). Comparison between vignettes will depend on attribute and level specification of each experiment. Analyses will be completed with and without respondents failing a ‘rationality’ test.

Marginal rates of substitution (the rate at which respondents are willing to give up a unit change in one attribute in exchange for a unit change in another while maintaining the same level of utility) will be calculated using each quantitative attribute as the value attribute with bootstrapped confidence intervals (1000 reps).

Preference heterogeneity will be assessed by estimating a mixed logit model, which will include random parameters for the attributes, and interactions between attributes and respondent characteristics.^91^ A-priori characteristics of interest are: (1) emergency care for epilepsy in the past 12 months (paramedic and/or ED visit), (2) social deprivation (with participants grouped according to how socially deprived the area is within which they live); (3) whether or not they have seen an epilepsy specialist within the prior 12 months (which they should have according to NICE guidelines^88^ given they will all have uncontrolled epilepsy); and (4) whether they or the person they know in the case of carers, self-reports an intellectual disability.

‘Utility scores’ for different ACP configurations and significantly different populations will be calculated and ranked accordingly. Their uptake under different seizure scenarios will be estimated.

All analyses will be conducted in STATA V.11.

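### Only ED visitors may complete the DCE face to face, so a mode-related difference in choice consistency may be read as a preference difference between visitors and non-visitors

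*Protocol article*

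**What the plan says.** All references are to Stage 2b of the protocol article.

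- **Design.** People with uncontrolled epilepsy and no ED visit in the last 12 months "will be asked to visit an online survey page and complete the DCE questionnaire using their own internet enabled devices". Patients who did visit an ED "will have the additional option of completing the DCE during a face-to-face appointment with a researcher who will provide an internet enabled device". The reason given is access: "Due to potentially greater social disadvantage".
- **Recruitment, Box 1.** The sample is doubled for this contrast. The text begins "As an objective was to describe and compare care preferences of two subgroups" and goes on to require 174 patients (and associated carers) in each group.
- **Analysis.** Each vignette is analysed separately. Heterogeneity is assessed in a mixed logit with random parameters and "interactions between attributes and respondent characteristics". Recent emergency care for epilepsy is the first of four characteristics named in advance. Utility scores for "different ACP configurations and significantly different populations will be calculated and ranked accordingly", and uptake is then estimated under the different seizure scenarios. Marginal rates of substitution with bootstrapped intervals are also planned, but the text does not say that they will be used to compare groups.

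**The concern.** A logit coefficient is the product of a preference weight and a scale factor, and scale is higher when respondents choose more consistently. Two groups with the same preferences but different consistency have different coefficients, all stretched by the same factor. An attribute-by-group interaction then departs from zero although nobody values the attributes differently. Random parameters and a panel error component do not by themselves separate a group difference in scale from one in preference.

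A researcher at hand could plausibly change consistency, for example by clarifying the task or holding attention. That option is open on one side only of the contrast that determined the sample size. Two outputs are exposed: the stated comparison of preferences between visitors and non-visitors, and any uptake estimate made separately for the two groups, because logit uptake depends directly on scale.

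**Working it through.** **1. The plan's sample size.** Box 1 uses Orme's rule with t = 9 tasks, a = 2 alternatives and c = 3 levels: n = 500 × 3 / (9 × 2) = 83.3, so 84. Two of three scenarios each: 84 × 3/2 = 126. This is raised to 150 by judgement, then to 174 for about 15% missing data (150 × 1.15 = 172.5; 150 / 0.85 = 176.5). Two groups: 2 × 174 = 348. The figure reproduces.

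**2. Information per vignette.** 174 × 0.85 × 2/3 = 98.6, so about 99 complete respondents per group per vignette.

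**3. Effect of mode-related scale on the interactions.** I simulated 100 respondents per group and nine binary choices each, with identical preferences in both groups.

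- From the plan: nine tasks, two alternatives, five attributes (within the planned four to six), and roughly the sample in step 2.
- Assumed: coefficients 0.6, 0.5, 0.4, 0.3 and 0.2; two-sided 5% level per coefficient; the share of visitors answering face to face; and the ratio of face-to-face to online scale.
- Model: plain binary logit with five main effects and five group interactions, 600 runs per setting (Monte Carlo standard error about 0.02 or less).

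| Share face to face | Scale ratio | P(at least one of 5 interactions significant) | P(ratio of two coefficients differs by group) |
|---|---|---|---|
| none | 1.0 | 0.24 | 0.02 |
| half | 1.3 | 0.31 | 0.03 |
| half | 1.5 | 0.42 | 0.03 |
| half | 2.0 | 0.80 | 0.04 |
| all | 1.3 | 0.61 | 0.04 |
| all | 1.5 | 0.90 | 0.04 |
| all | 2.0 | 1.00 | 0.05 |

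The first row is not a mode effect. It is about what five separate 5% tests give: 1 − 0.95^5 = 0.23. The rise above it is the mode effect. The last column, a test on the ratio of the two largest coefficients, stays at or below 5% throughout, because scale cancels in a ratio.

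**4. Effect on uptake.** Take an assumed utility gap of 1.0 between an ACP and its alternative. Uptake is 1 / (1 + exp(−scale × 1.0)): 73.1% at scale 1, 78.6% at 1.3, 81.8% at 1.5 and 88.1% at 2.0. If half of visitors answer face to face, the group average is (73.1 + 78.6)/2 = 75.9%, (73.1 + 81.8)/2 = 77.5% or (73.1 + 88.1)/2 = 80.6%. Visitors' uptake would appear about 3 to 7.5 points above non-visitors', with the same preferences.

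**5. Effect on rank order.** Multiplying every utility by the same positive constant leaves the order of ACP configurations within a group unchanged.

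**The case against.** The case on the other side is substantial.

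- **Overlap is partial.** Face to face is optional, so visitors will probably be mixed in mode. The option is worded for patients, and the text does not extend it to Group 1 carers. The researcher supplies an internet-enabled device, so the questionnaire appears to be the same. The modelled characteristic also counts paramedic contact, which is wider than the group offered the option. All of this stands, and it dilutes the effect. It does not remove it, because every face-to-face patient still falls on the emergency-care side of the contrast.
- **Safeguards exist.** Marginal rates of substitution are scale-free, and the analyses with and without respondents failing the rationality test bear on consistency. That also stands, but neither is tied to the group comparison, which is specified through interactions.
- **The size is assumed.** No document gives the face-to-face share, the scale ratio or its direction, and the simulation used a simpler model than the planned mixed logit. At a ratio of 1.3 with half face to face the rise is small.
- **The article is condensed.** Mode adjustment and scale handling may sit in an analysis plan that is not shown. Their absence here is therefore not an error in itself. The point rests on what the article does fix: a mode option restricted to one comparison group, and a comparison made on interaction coefficients.

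A reader might also infer that subgroups will be declared whenever a single raw coefficient is significant, and that chance alone will then create false subgroups. The documents do not support this. The phrase "as indicated by the significance of the coefficients and their size" concerns the importance of attributes within a vignette. For subgroups the article speaks only of interactions and significantly different populations, names no test, and would be consistent with a joint test. Multiplicity control may be set out elsewhere.

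**Conclusion.** The concern holds in a limited form. Completion mode is partly confounded with the visitor versus non-visitor contrast, and the comparison as described cannot tell a mode-related difference in consistency from a difference in preference. The result may, not will, be misread. With identical preferences and half of visitors face to face, the chance of at least one significant group interaction in one vignette goes from about 0.24 to 0.31–0.80 over assumed scale ratios of 1.3 to 2.0. Under the same assumptions, and a utility gap of 1.0, apparent uptake among visitors shifts by about 3 to 7.5 points.

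It would be tempting to conclude that mode will produce false ACP rankings for the Stage 3 delegates. That does not follow: a pure scale difference leaves the ranking within each group unchanged. What is at risk is the claim that the groups differ, and the group-specific uptake figures. The correction is worth making because it protects a stated objective at little cost.

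**What to change.** Keep the face-to-face option; its access rationale is sound.

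1. Record completion mode for every respondent.
2. Base the visitor versus non-visitor comparison on scale-free quantities (the planned marginal rates of substitution, or relative attribute importance), or on a model with a scale parameter for group and mode. Both modes should occur among visitors, which is what allows group and mode to be separated.
3. Use one joint test per characteristic per vignette to judge whether preferences differ.
4. Where uptake is reported by group, take it from the scale-adjusted model, since a ratio comparison does not correct uptake.
5. Repeat the comparison in online completers only, as a sensitivity analysis.

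The cost is one recorded variable and a few extra model fits, with no additional appointments. The online-only repeat has a price that should be stated with its results. It drops the more disadvantaged respondents, for whom the option was created, so it exchanges a mode difference for possible selection. If half of visitors answer face to face, it also leaves only about 98.6 / 2 = 49 visitors per vignette. It should support the main comparison, not replace it.

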##### Recruitment

General Practices in North-West England will identify potential patient participants by searching their epilepsy registers.^86^ Practices will be recruited with the help of the NIHR Clinical Research Network North West Coast. Practices will send ostensibly eligible patients invitation packs via ‘Docmail’ and a repeat invite 2 weeks later to those not responding. Patients not wishing to participate will be encouraged to notify the team and detail their reasons. Eligibility criteria are in table 1.

A definitive sample size calculation depends on the finalised design of the DCE.^87^ To permit decisions regarding recruitment to be made in the meantime we anticipated the design and calculated the required sample size by using Orme’s^88^ formula. Full details are provided in box 1. This indicated 348 PWE (or associated informal carers) would be required, comprising data 174 patients (or associated carers) who have visited ED in the prior 12 months and 174 patients (or associated carers) who have not.

Box 1Sample size calculation for discrete choice experimentsFormula used and factors considered in estimating likely sample size requiredOrme’s formulae: (*n***t***a*)/ *c* must be ≥500, where *n* is number of respondents, *t* number of tasks, *a* number of alternatives per task, and *c* number of analysis cells (for main effects, the largest number of levels for any one attribute).Anticipated discrete choice experiments (DCEs) to involve participants being asked to make (*t*) nine separate choices between (*a*) two care packages and (*c*) three would be maximum attribute levels. Thus, Orme’s formula indicated complete data from n=84 needed.Intend to complete DCEs for three different seizure scenarios, but participants would only complete two, therefore 126 participants required.To allow for variation in the finalised number of choice tasks and levels we increased this to 150 and further inflated it to 174 to accommodate for ~15% of missing data experienced by prior epilepsy DCEs.As an objective was to describe and compare care preferences of two subgroups (patients (and associated carers) who have visited an ED in the prior 12 months versus patients (and associated carers) who have had a seizure in the prior 12 months, but have not visited an ED), 174 patients (and associated carers) who have visited ED in the prior 12 months and 174 patients (and associated carers) who have not, will need to be recruited.Total sample size, thus n=348.

Based on responses to prior health DCEs^89^ and studies with PWE,^16 24^ we anticipate 30%–60% of those invited will agree to participate. An average English GP practice^90^ will have 24 PWE aged ≥18 on their register who have experienced ≥1 seizure in the prior 12 months,^9^ with 10 having visited an ED during that period.^12–14^ Governed by the need to recruit a subgroup of 174 PWE who have visited ED in the prior 12 months, 29–58 general practices will be required.

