## Abstract

**Introduction:**

Emergency department (ED) visits for epilepsy are common, costly, often clinically unnecessary and typically lead to little benefit for epilepsy management. An ‘Alternative Care Pathway’ (ACP) for epilepsy, which diverts people with epilepsy (PWE) away from ED when ‘999’ is called and leads to care elsewhere, might generate savings and facilitate improved ambulatory care. It is unknown though what features it should incorporate to make it acceptable to persons from this particularly vulnerable target population. It also needs to be National Health Service (NHS) feasible. This project seeks to identify the optimal ACP configuration.

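### Stage 2b separates ED visitors from non-visitors only where they differ significantly, so an overall uptake or ranking may describe the 50:50 recruitment quota rather than the people whose 999 calls an ACP would meet

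*Protocol article*

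**What the plan says.** The Stage 2b Recruitment section asks for "174 patients (or associated carers) who have visited ED in the prior 12 months and 174 patients (or associated carers) who have not", 348 in total. Box 1 gives the reason for equal groups: "As an objective was to describe and compare care preferences of two subgroups". The Design section describes the people sought as "A representative sample of PWE and informal carers who have visited ED in the last 12 months, as well as those at risk".

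The Stage 2b Analysis section states: "Data for the different seizure vignettes will be analysed separately using an error components logit model". It names no split by ED-visit group for that model. A mixed logit model with interactions then examines heterogeneity. Its first listed characteristic is emergency care for epilepsy in the past year, counting paramedic contact as well as ED visits. Utility scores are to be calculated and ranked for the ACP configurations and for populations that differ significantly, and uptake is to be estimated by seizure scenario. The Aims and the Stage 2b Purpose also promise subgroup differences in uptake.

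Three other statements bear on the target population:
- The Abstract describes an ACP as a pathway that "diverts people with epilepsy (PWE) away from ED when" a 999 call is made.
- The Introduction's section on ACPs says that about 90% of people visiting ED for seizures arrive by ambulance, and that crews advise conveyance for almost everyone they see for a suspected seizure.
- The Recruitment section gives 24 adults with a recent seizure on an average practice register, "with 10 having visited an ED during that period".

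**The concern.** Equal groups are a good choice for a contrast between visitors and non-visitors. They are not a picture of any population in which an ACP would run. The mix matches neither the register nor the flow of 999 calls. It does no harm while results are kept separate by group, but that separation is made to depend on a significance result. If the groups differ and the test misses it, the natural reading is one score and one uptake figure for everyone, and the recruitment ratio then sets the answer.

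This matters because the configurations, ranked by service-user preference, open the Stage 3 workshops at which one ACP is to be prioritised. The Introduction also says that in the only epilepsy ACP reported so far, fewer than 10% of eligible people seen by paramedics were put onto it. Uptake among people who meet paramedics is therefore the quantity of interest.

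**Working it through.** **1. The plan's own figures.** Box 1 assumes "nine separate choices between (*a*) two care packages and (*c*) three would be maximum attribute levels".
- Orme's rule: n = 500 × 3 / (9 × 2) = 83.3, so 84.
- "Intend to complete DCEs for three different seizure scenarios, but participants would only complete two, therefore 126 participants required": 84 × 3/2 = 126.
- This is raised by judgement to 150, then for about 15% missing data. 150 × 1.15 = 172.5 and 150 / 0.85 = 176.5, so 174 is reasonable.
- Two groups: 2 × 174 = 348.
- Practices: 174 / (10 × 0.60) = 29 and 174 / (10 × 0.30) = 58, as stated.

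The sample size reproduces. No significance level, power or effect size enters it.

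**2. Respondents per group and vignette.** Each respondent completes two of three scenarios, so 174 × 2/3 = 116 per group see each vignette. After 15% missing data, 116 × 0.85 ≈ 99 remain. The article gives no expected difference between groups, so the power of the test that would trigger separate scores cannot be derived.

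**3. Weight of non-visitors under three targets.**
- Unweighted pool: 174/348 = 50%.
- Persons on the register: 14/24 = 58.3%.
- 999 calls: a conveyed call belongs to a visitor by definition, so the non-visitor share = (1 − conveyance rate) × (share of non-conveyed calls made by non-visitors). Letting the second factor run from 0 to 1, the share is 0–10% at an assumed 90% conveyance, 0–20% at 80% and 0–30% at 70%. The article gives no rate, only that conveyance is advised for almost everyone.

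**4. Effect on uptake.** Treating the pooled figure as an average of the two groups, it differs from the visitors' figure by half the gap: 5, 10 or 15 points for gaps of 10, 20 or 30. Assumed examples, with a non-visitor weight of 0–30% for the call-weighted column:

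| Visitors | Non-visitors | Pool 50:50 | Register 10:14 | Call-weighted |
|---|---|---|---|---|
| 40% | 60% | 50% | 51.7% | 40–46% |
| 60% | 50% | 55% | 54.2% | 57–60% |
| 50% | 50% | 50% | 50% | 50% |

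The sign follows the gap, and with no gap the mix is irrelevant.

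**5. Cost of reweighting.** Register weights are (10/24)/0.5 = 0.833 for visitors and (14/24)/0.5 = 1.167 for non-visitors. The approximate variance inflation is (0.833² + 1.167²)/2 = 1.028, or about 1.4% on the standard error. Using half the sample, as within one stratum or when most non-visitors get zero weight, multiplies the standard error by √2 = 1.41.

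**The case against.** The strongest reply is that the article never announces a single pooled uptake. It pairs uptake with subgroup differences in the Aims and the Stage 2b Purpose, makes emergency care in the past year its first a-priori characteristic, and provides for separate scores. Uptake within a stratum does not depend on the quota. This stands. A reader might infer that uptake is simply one figure counting every respondent once; the text does not say so.

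It is also fair that weights for predicted uptake are usually left to a fuller analysis plan, so their absence alone is no fault. What remains is something the article does state: separate scores are tied to a significant difference.

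A large gap is the case most likely to be detected, so the worst errors are partly self-limiting. That is true, but detection is not assured in groups sized without regard to power.

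Three stronger readings also fail:
- Non-visitors are not people who never call 999. Table 1 excludes ED visits in Group 2, not paramedic attendance without conveyance.
- The quota does not under-represent visitors on every scale. Per person on the register (10 of 24, 41.7%) it slightly over-represents them. The imbalance runs the other way only when calls are counted.
- Nothing shows that uptake would be overstated. The Introduction reports that some patients dislike being taken to ED and others want urgent care, but does not compare visitors with non-visitors on this.

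**Conclusion.** The point holds as a limited one. The quota is sound for its stated purpose, and the planned subgroup work covers much of the problem. The weak place is the conditional split: after a non-significant result, overall utility ranks and uptake would carry a 50:50 mix that represents neither the register nor the 999 calls an ACP would meet.

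The size is half the true gap in uptake between the groups. That rests on assumed gaps, on assumed conveyance rates for the call-based comparison, and on treating the pooled model's prediction as close to the average of the groups. Ranks change only if the two groups order the configurations differently, which the documents neither show nor exclude.

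**What to change.** Keep the 174:174 quota, and change the Stage 2b Analysis wording as follows.

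1. Report utility ranks and uptake for each seizure scenario separately for respondents with and without ED or paramedic contact in the past 12 months, whatever the significance result. Because the quota is set on ED visits alone, apply the quota correction within the contact stratum as well.
2. Name the target population for any overall figure and reweight from the quota. For a per-person figure, use the 10:14 register ratio. State that this is a planning average, and that Group 2 requires a seizure with loss of awareness, so 14 may be too high.
3. Add a version weighted by reported emergency contacts as a sensitivity analysis, not as the headline, since the choice between persons and calls is debatable. State whose contacts count for a carer, and how a patient and carer reporting the same contacts avoid being counted twice.

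Recruitment does not change, and service use is already collected. Register weighting costs about 1.4% in standard error. Estimates within a stratum of half the sample have standard errors about 41% larger than the pooled ones. Contact weighting costs at least that much if most non-visitors get zero weight, and more if contacts are concentrated in a few people. The contact counts are self-reported.
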